
### Assessment

Assessments take place 5–21 days before the surgery (baseline, T0), preoperatively on the day of hospital admission after the psychological intervention (T1), 7 days after surgery (T2) and 6 months after surgery (T3) (for an overview, see figure 2). Psychological data will be collected through questionnaires (eg, regarding disease-related impairment, quality of life, depression and anxiety) and takes place online via the secure web-based survey platform UniPark (https://www.unipark.com/). At each assessment point (T0–T3), completion of the psychological questionnaires will require approximately 30 min. Participants are encouraged to complete them online via UniPark, although paper-based versions may be provided by clinical staff in cases of technical difficulties, and retention is supported through personalised email invitations, reminder emails and phone calls. These strategies have been shown to enhance compliance and reduce attrition,^46^ helping to ensure complete data collection across all time points. Patients will be asked to complete the questionnaires and to contact study therapists if they have any questions. For a detailed overview, see the online supplemental table S2, which shows the applied questionnaires, biological parameters and case report forms (CRFs). Furthermore, semistructured interviews with a small subset of CABG patients (up to N=12) will be conducted on a voluntary basis after surgery to retrospectively explore preparation needs and qualitatively assess the intervention. Interviews (30–45 min) will be audio-recorded, transcribed and analysed using qualitative content analysis.^47^ All data will be anonymised.

### Biological markers

Proinflammatory markers like CRP and interleukin-6 (IL-6) can induce depressive-like symptoms and alter neurophysiological processes.^48^ In PSY-HEART-I, the ‘EXPECT’ intervention reduced postoperative inflammation (interleukin-8) compared with standard treatment, with baseline inflammation moderating long-term outcomes.^49 50^ Biological factors are vital in understanding cardiovascular outcomes, especially since atherosclerosis, a common cause of CHD, raises inflammatory markers.^51 52^ The effectiveness of internet-based interventions in improving inflammation status remains unclear, warranting further research. HRV predicts heart surgery complications.^53^ This feasibility study will collect blood samples and HRV data at four timepoints: baseline (T0), postintervention (T1), postsurgery (T2) and 6 months postsurgery (T3) (see online supplemental table S2). To enhance feasibility, postoperative collection of biomarkers will be scheduled for postoperative day 7 or at the time of hospital discharge, whichever occurs first, to avoid requiring patients to return for bloodwork and HRV assessment after discharge.

#### Collection procedure

Blood samples will be taken outside of fasting periods to examine plasma levels of inflammatory markers (CRP, IL-6) at each assessment point (T0–T3). Patients will be either sitting or lying down to minimise the impact of movement or physical activity on the results. Prior to blood collection, patients will rest for 30 min. Once collected, blood will be placed into polyethylene tubes with EDTA as an anticoagulant (S-Monovette; Sarstedt, Nümbrecht, Germany), then promptly transported on ice to the laboratory. There, samples will be centrifuged at 2000 g for 10 min in a refrigerated centrifuge (4°C). Plasma aliquots will be stored at −80°C until analysis. Blood samples will be obtained by the study team in Marburg and sent to Essen for analysis by [name] and his team at the Institute of Medical Psychology and Behavioral Immunobiology at the University Clinic Essen. Variability coefficients will be calculated for both intra-assay and interassay precision. The procedure will remain consistent across all treatment groups. Once analysis is complete, blood samples will be discarded. Heart rate will be recorded as beat-to-beat intervals using Polar H10 sensors with chest straps and the Elite HRV application on Android phones at 1000 Hz.^54^,^56^ Beat-to-beat intervals will measure the time between successive R-spikes. To analyse HRV indices such as RMSSD (‘Heart Rate Variability’, 1996), we will record at least 5 min of heart rate activity while patients are sitting. Data will be collected and documented through an electronic CRF (eCRF/EDC-System) hosted by KKS Marburg, with secure web-based data entry (HTTPS (TSL/SSL) and supplementary outcome information, including any complications.

### Data analysis plan

The hypotheses of primary interest refer to the feasibility of the study design and acceptability of the iEXPECT intervention as an internet-based intervention, which will be assessed based on three criteria:

Feasibility of the study design is assumed if at least one participant per week per centre can be recruited (approximately 160 participants from three centres over 53 weeks), and >49% of all randomised patients provide complete data for the 6-month follow-up assessments, including biomarkers. The recruitment threshold of ≥1 participant per centre per week was based on the assumption that a Phase III trial with *X* centres could achieve its enrolment target within a recruitment period of *Y* under this rate. The ≥49% randomisation threshold was chosen to reflect an acceptable screening-to-randomisation efficiency while accounting for expected attrition. The proportion of patients with complete data for the 6-month follow-up assessments (including biomarkers) will be reported as a point estimate per group. Two-sided 95% CIs will be given.Feasibility of the internet-based intervention is assumed if >75% of the randomised patients in each iEXPECT arm complete at least 1 (>0) online module before the surgery. The completion rate will be reported as a point estimate per intervention group, and two-sided 95% CIs will be provided. To assess whether time to surgery influences outcome criterion 2 (completion of at least one online module before surgery), a sensitivity analysis will be considered.Acceptance will be assessed by self-report ratings at the end of each online module and with the CSQ-I after the intervention (T1) and the 6 months follow-up (T3). To evaluate a session’s/the intervention’s enjoyableness, usefulness and effect on daily social functioning using a 5-point scale (1=fully disagree, 2=disagree, 3=not sure, 4=agree, 5=fully agree; examples for items: ‘This session/intervention was useful and sensible’, ‘I would recommend this session/intervention to others’, ‘This session/intervention lived up to my expectations’). Acceptance of the internet-based intervention is assumed if the mean rating for overall acceptance/satisfaction with the intervention (calculated after completion of each of the four modules) exceeds 3.4. This threshold was chosen to reflect a tendency toward agreement rather than neutrality (>3=‘not sure’) and is supported by prior data^12^ suggesting an expected mean of 3.7 (SEM=0.14), making >3.4 a conservative and statistically robust criterion. Each intervention group will be analysed separately and mean rating of acceptance/satisfaction with the intervention will be presented for each online module. An overall mean rating across the four modules/predefined timepoints of assessment will be calculated.

Baseline characteristics will be presented by group. For categorical variables, the number of patients per category will be reported as well as the category proportion. The number of missing values will also be presented. For continuous variables, mean and SD will be reported. Primary and secondary outcome variables will be analysed in the same way at the predefined timepoints. Secondary outcomes will be analysed descriptively to identify relevant trends, inform intervention refinement and guide power calculations for a future Phase III trial. While the study is not powered to detect efficacy, exploratory correlation and regression analyses may be performed to examine relationships among secondary outcome variables and to generate hypotheses for subsequent confirmatory research.

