**Methods and analysis:**

In this three-arm, multicentre randomised controlled trial, 160 patients undergoing elective coronary artery bypass graft surgery are randomised to: (a) standard of care (SOC); (b) SOC plus iEXPECT with phone-based guidance (iEXPECT enhanced) or (c) SOC plus iEXPECT with email-based guidance (iEXPECT limited). The intervention includes four 20 min online modules addressing surgical benefits, side effects and coping strategies. Modules are accompanied by personalised guidance provided through feedback on each module via email or telephone (three before surgery, three booster sessions at 6, 12 and 18 weeks postsurgery). Assessments occur at baseline (5–21 days before surgery), preoperatively (day before surgery), 7 days postsurgery and 6 months later. Primary feasibility outcomes include recruitment (≥1 participant/week/centre), retention (≥49% completing 6-month follow-up including biomarkers) and engagement (≥75% completing ≥1 presurgery module). Acceptability is measured by self-reported enjoyment, usefulness and impact, with acceptance defined as mean scores >3.4 (5-point Likert scale) and CSQ-I ratings. Secondary outcomes include psychological measures, inflammatory markers and heart rate variability.

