### Sample size and study power

This feasibility study will explore the rate of completing at least one online module before surgery (outcome criterion 2). This will provide valuable information on what can be expected in a future Phase III trial. As one proportion, CIs are used to estimate a population proportion, sample size calculation is based on a CI approach. For a future Phase III trial, we want to assure that at least 75% of the patients in an iEXPECT group will complete at least one online module before surgery. In our study, we expect a completion rate of 84% in each intervention group, because it provides a meaningful buffer above the 75% feasibility threshold and ensures that the lower bound of the 95% CI will remain above this criterion, while keeping the required sample size feasible. Using a two-sided 95% CI with a lower CI limit of 75%, and an expected completion rate of 84%, we found that each intervention group should have at least 64 patients for the study. As the primary focus lies on assessing the feasibility of the online interventions, the calculated sample size is required for each of the two intervention groups. Since this is a feasibility trial and not designed to detect statistically significant differences between groups, we decided to allocate only half as many participants (N=32) to the SOC group. We consider this sample size sufficient to provide preliminary insights into secondary outcomes within the SOC group. Accordingly, patients will be randomised in a 2:2:1 ratio across the two intervention arms (iEXPECT enhanced: iEXPECT limited) and the SOC arm, resulting in a total sample size of N=160. The sample size calculation was performed using PASS V.14 software (NCSS; www.ncss.com).

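### The primary engagement criterion carries two inequalities (≥75% and >75%), and it is decided on the observed rate although the arms were sized on the lower 95% limit

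*Protocol article*

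**What the plan says.** The engagement criterion appears in three places in the protocol article.

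- **Abstract, Methods and analysis:** "engagement (≥75% completing ≥1 presurgery module". The inequality is non-strict, and the abstract does not say that it applies to each arm.
- **Data analysis plan, second criterion:** "Feasibility of the internet-based intervention is assumed if >75% of the randomised patients in each iEXPECT arm" complete at least one module before surgery. The inequality is strict, applies to the observed proportion and must hold in each arm. On uncertainty it adds: "The completion rate will be reported as a point estimate per intervention group, and two-sided 95% CIs will be provided". The interval is reported but is not part of the rule.
- **Sample size and study power:** the stated aim is that "we want to assure that at least 75% of the patients in an iEXPECT group will complete at least one online module before surgery". The calculation is described as "Using a two-sided 95% CI with a lower CI limit of 75%, and an expected completion rate of 84" per cent, giving at least 64 patients per intervention arm. The choice of 84% is justified partly because it "ensures that the lower bound of the 95% CI will remain above this criterion".

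For acceptance, the abstract and the data analysis plan both require a mean above 3.4. The plan cites an expected mean of 3.7 (SEM 0.14), "making >3.4 a conservative and statistically robust criterion".

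**The concern.** There are two separate faults in one primary criterion.

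First, the abstract and the analysis plan disagree on whether exactly 75% is a pass. With 64 per arm this value can occur, so the verdict could depend on which sentence is cited.

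Second, the arms were sized against one standard (the lower confidence limit) and are judged against a weaker one (the point estimate). The sample size section speaks of assuring at least 75%. A rule on the observed rate gives no such assurance, because an arm whose true rate sits at the threshold passes nearly half the time. If this is left open, the standard can be chosen after the data are seen, and an arm may be described as having shown at least 75% when its interval extends well below that.

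**Working it through.** **Inputs.** Threshold 75% and the per-arm rule come from the data analysis plan. Expected rate 84%, two-sided 95% interval, lower limit 75% and n = 64 per arm come from the sample size section. Acceptance: 3.7, SEM 0.14 and threshold 3.4 come from the data analysis plan. Figures for both arms assume that the arms are independent with the same true rate.

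**1. Reproducing the plan's 64.** The Wald interval for one proportion gives n = 1.96² × 0.84 × 0.16 / (0.84 − 0.75)² = 63.74, rounded up to 64. The lower limit at an observed 84% is then 0.84 − 1.96 × √(0.84 × 0.16 / 64) = 0.7502. The stated figure reproduces, and it is the simple Wald figure. The same target needs 89 per arm with the Wilson interval and 94 with Clopper-Pearson.

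**2. The two inequalities.** 0.75 × 64 = 48 exactly. So 48/64 passes the abstract (≥75%) and fails the analysis plan (>75%). The binomial probability of exactly 48 is 11.5% at a true 75%. At a true 84% it is 97.9% − 95.8% = 2.1%.

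**3. Observed rate against lower limit, n = 64.**

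| Completers | Observed | Wald lower 95% limit |
|---|---|---|
| 49 | 76.6% | 66.2% |
| 50 | 78.1% | 68.0% |
| 51 | 79.7% | 69.8% |
| 52 | 81.3% | 71.7% |
| 53 | 82.8% | 73.6% |
| 54 | 84.4% | 75.5% |

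Counts of 49 to 53 pass the analysis plan's rule and miss the sizing target. With Clopper-Pearson this zone is 49 to 55 (the lower limit at 55/64 is 74.98%).

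**4. Chance of passing** (exact binomial tails; both arms = square of the per-arm value).

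| What decides | Needed of 64 | True 70%: per arm / both | True 75%: per arm / both | True 84%: per arm / both |
|---|---|---|---|---|
| Observed rate >75% | 49 | 15.6% / 2.4% | 45.2% / 20.4% | 95.8% / 91.8% |
| Wald lower limit >75% | 54 | not computed | 5.1% / 0.3% | 55.1% / 30.3% |
| Wilson lower limit >75% | 55 | not computed | 2.5% / 0.1% | 41.5% / 17.2% |
| Clopper-Pearson lower limit >75% | 56 | not computed | 1.1% / 0.01% | 28.5% / 8.1% |

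The 55% follows from how the arm was sized. The calculation puts the lower limit at 75% when the observed rate equals its expected value, and sampling variation takes the observed rate below that value in roughly half of trials.

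**5. Acceptance.** (3.7 − 3.4) / 0.14 = 2.14, so the threshold lies 2.1 SEM below the expected mean. The prior lower 95% limit is 3.7 − 1.96 × 0.14 = 3.43, just above 3.4.

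**The case against.** The best defence is that the lower limit is only a sizing target. The sample size section says that confidence intervals serve to estimate a proportion, and nowhere makes the limit a decision rule. Judging a feasibility trial on an estimate with its interval alongside is legitimate, and the plan does report that interval per arm. This stands, so a reader who infers that the plan breaks its own decision rule goes too far. It does not rescue the statements that the design assures at least 75% and keeps the lower bound above it.

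The rule also requires both arms to pass, which makes it stricter than the per-arm figures suggest: at a true 70% both pass only about 2% of the time. That stands as well. It would be wrong to say that clearly inadequate engagement is often declared feasible.

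The clash of inequalities matters only at exactly 75%, which needs an arm size divisible by four and is unlikely (2.1% per arm) if the true rate is 84%. It is a small fault, but it sits on a primary threshold at the planned arm size.

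Three further readings are tempting and unsupported:

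- **That acceptance has the same contradiction.** It is >3.4 in both places, and nothing was sized on an acceptance limit. The plan also justifies 3.4 as lying above the neutral score of 3. A confidence interval for a mean is a detail that an article may leave to the full protocol.
- **That this rule alone decides on Phase III.** The article calls the trial a precursor, has three criteria and states no go/no-go rule.
- **That a lower-limit rule with a hard stop is required.** That is a design choice, and at n = 64 an expensive one.

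**Conclusion.** The point holds for engagement. The abstract and the analysis plan give opposite verdicts at 48/64. The observed-rate rule does not deliver the standard used for sizing: 49 to 53 of 64 pass with Wald lower limits of 66% to 74%, and a true 75% passes 45% of the time per arm, about 20% for both. The claim that an expected 84% secures a lower bound above 75% is wrong, since this happens in about 55% of trials per arm and 30% for both by Wald, and less often with the other intervals.

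These figures rest on exactly 64 randomised per arm, binomial counts and, for the joint values, independent arms.

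For acceptance only the description is open to challenge. A threshold 2.1 SEM below the expected mean is not conservative relative to the prior data cited for it, but the rule itself is consistent.

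**What to change.** 1. Use >75% in the abstract as in the data analysis plan, and say in both that it applies to each arm.
2. State in the data analysis plan whether the observed rate or the lower 95% limit decides the second criterion, and name the interval method. The method matters: the count required under a lower-limit rule runs from 54 to 56 of 64.
3. **If the observed rate decides:** remove the language of assurance from the sample size section and give the rule's operating characteristics instead (per arm / both: 16% / 2% at a true 70%, 45% / 20% at 75%, 96% / 92% at 84%). Describe an arm whose estimate exceeds 75% but whose lower limit does not as not having shown at least 75%.
4. **If the lower limit decides:** state the reduced chance of passing at a true 84%, which is 55% per arm and about 30% for both by Wald, or about 29% and 8% by Clopper-Pearson.
5. For acceptance, at most report a 95% interval with the mean and drop the description of 3.4 as conservative and robust.

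Items 1, 3 and 5 cost only wording. Item 4 changes the trial's chance of success: at a true 84%, both arms passing falls from about 92% to 30% or less, unless the sample is enlarged.

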In a previous step, the traditional face-to-face ‘EXPECT’ intervention for expectation optimisation was adapted into an online format (iEXPECT). The present study—the iHEART trial—aims to test the feasibility of the study design and the acceptability of the online, preoperative, guided psychological iEXPECT intervention. Specifically, the primary objectives are to evaluate (1) the feasibility of implementing the study design across multiple sites, similar to the PSY-HEART-II trial, (2) whether patients are able and willing to engage with the intervention as intended and (3) the acceptability of the iEXPECT intervention from the patients’ perspective. Given the uncertainty around the optimal level of guidance for online interventions,^18 19^ this study will also explore two variations of the online intervention, each offering different levels of therapist support (enhanced vs limited interaction). Secondary outcomes include psychological and physiological measures that will be analysed descriptively per group. Biomarkers will be collected to assess the feasibility of obtaining inflammatory markers and heart rate variability (HRV).

This feasibility trial also serves as a precursor to a larger future study (Phase III trial) aimed at evaluating the efficacy of the iEXPECT intervention. If successful, the iHEART trial could counteract the previous barriers and could thus improve access to better healthcare for patients undergoing heart surgeries.

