Following modules (1–3) completion, patients receive personalised guidance via telephone call (iEXPECT enhanced) or via email (iEXPECT limited) on the content from the iHEART study team. All modules (at least 1–3) should be completed by no later than 1 day before the heart surgery.

CABG, coronary artery bypass graft; CHD, coronary heart disease; iEXPECT, expectation manipulation online intervention.

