### iEXPECT intervention

Participants in the intervention groups receive an email invitation with their patient IDs to access the online study platform (https://www.minddistrict.com/de-de) and instructions for use. They can progress through the intervention modules and contact the study team with questions.

The internet-based iEXPECT intervention with four modules before, and three guided booster sessions after surgery can be done from home in the participants’ own time (for an overview, please see the intervention schedule in figure 2). Participants receive semistructured guidance via email or phone (~10-15 min) within 1–2 working days after each module, reinforcing strategies and addressing challenges. Noteworthy, patients in the iEXPECT enhanced group will receive more tailored guidance as the personal contact via telephone allows study therapists to directly interact with the patients to ensure patients’ complete understanding. Furthermore, a second placebo mechanism (besides expectations) is used: positive interaction between patient and therapist.^23^

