#### Feasibility

Feasibility is defined across two dimensions, namely (1) feasibility of the study design, referring to the successful recruitment and retention of participants across multiple study sites (outcome criterion 1) and (2) feasibility of intervention implementation, referring to the patients’ engagement with the iEXPECT modules prior to surgery (outcome criterion 2). These outcomes reflect whether the trial can be operationalised as intended and whether participants are willing and able to engage with the digital intervention components.

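### Criterion 2 measures uptake of iEXPECT (one module completed) and cannot show the engagement as intended that objective 2 asks about

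*Protocol article*

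**What the plan says.** The Introduction lists three primary objectives. The second is "whether patients are able and willing to engage with the intervention as intended".

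The section iEXPECT intervention describes the course: "The internet-based iEXPECT intervention with four modules before, and three guided booster sessions after surgery". Table 1 assigns surgical benefits, together with the platform welcome, to module 1, personal control to module 2, side effects and coping to module 3, and a summary to module 4. The note under Table 1 gives the only stated pre-surgery minimum: "All modules (at least 1–3) should be completed by no later than 1 day before the heart surgery".

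The Feasibility section, under Primary outcomes, describes feasibility of intervention implementation in the plural: "referring to the patients’ engagement with the iEXPECT modules prior to surgery (outcome criterion 2").

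The decision rule in the Data analysis plan is that feasibility is assumed if ">75% of the randomised patients in each iEXPECT arm complete at least 1 (>0) online module before the surgery", reported per arm with a two-sided 95% CI. The Abstract and the sample size section also use the one-module cut-off. On the effect of time to surgery on this outcome, the plan says only that "a sensitivity analysis will be considered".

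The sample size section states: "we expect a completion rate of 84% in each intervention group". It explains the 84% as a buffer above 75%. It does not explain why one module is the cut-off.

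**The concern.** The objective and its decision rule measure different things. The rule counts a patient as a success after any one module. Study design presents benefit expectations, personal control and coping as the three main components of the intervention, and Table 1 gives each its own module. A patient who stops after module 1 has met neither the second nor the third component, and can have had at most one of the three pre-surgery guidance contacts. Guidance is what separates the enhanced from the limited arm, so a one-module rule also says little about which level of support carries patients through the course.

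The article makes this trial the precursor to a Phase III efficacy trial. A positive result on criterion 2 would be evidence that patients start the programme. Read as an answer to objective 2, it would be taken as evidence that they receive it.

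**Working it through.** **Inputs.** From the sample size section: expected rate p = 0.84, lower limit L = 0.75, two-sided 95% CI, n = 64 per iEXPECT arm. From the Data analysis plan: pass if more than 75% of an arm complete at least one module. From the note to Table 1: minimum of modules 1–3 before surgery.

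**1. The plan's own figure.** With the normal-approximation interval, n = 1.96² × p(1−p)/(p−L)² = 1.96² × 0.84 × 0.16/0.09² = 63.74, rounded up to 64. The stated n reproduces.

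**2. Smallest pass.** 48/64 = 75.0% does not exceed 75%; 49/64 = 76.6% does. Modules 1–3 for 64 patients make 64 × 3 = 192 completions. If each of the 49 completes one module only, 49/192 = 25.5% are delivered. Counting all four pre-surgery modules, it is 49/256 = 19.1%. Nobody meets the modules 1–3 minimum, yet the criterion is met.

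**3. Stricter reading.** Suppose the lower confidence limit had to exceed 75%. At 54/64 (84.4%) the limit is 75.5%; at 53/64 it is 73.6%. The pass mark becomes 54, and delivery could still be as low as 54/192 = 28.1%.

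**4. A graded case (assumption).** The article gives no expected rate for modules 1–3. Assume that 84% complete module 1 and that a fraction c continues at each of the next two steps, so the modules 1–3 rate is 0.84 × c². The chance of passing is the exact binomial probability of at least 49 of 64.

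| c | Modules 1–3 rate | Chance one arm passes, current rule | Chance if the same >75% rule applied to modules 1–3 |
|---|---|---|---|
| 1.00 | 84.0% | 95.8% | 95.8% |
| 0.95 | 75.8% | 95.8% | 51% |
| 0.90 | 68.0% | 95.8% | 9% |
| 0.80 | 53.8% | 95.8% | below 0.1% |
| 0.70 | 41.2% | 95.8% | below 0.1% |

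The third column does not change with c, so the current rule carries no information on drop-off after the first module.

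**5. Precision of a modules 1–3 estimate at n = 64.** The widest half-width is at 50%: 1.96 × √(0.25/64) = 1.96 × 0.0625 = 0.1225, about 12 points.

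**6. What n = 64 cannot do.** If a lower limit of 75% were demanded of modules 1–3, the formula in step 1 gives 64 per arm at an expected 84%, 116 at 82% and 246 at 80%. It cannot be met at 75% or below. The 75% threshold should therefore not be carried over to modules 1–3 without its own justification.

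**The case against.** **The criterion is a declared choice.** One module is stated consistently in the Abstract, the Data analysis plan and the sample size section, and the last links it to what Phase III needs. The Feasibility section speaks of being willing and able to engage, which one module could be said to show. This stands as a reason to keep the criterion. It does not make the criterion an answer to objective 2.

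**The note to Table 1 is not a definition.** It says what should be completed and by when; it does not say that engagement as intended means modules 1–3. That is correct. It is, however, the only minimum the article gives, and it belongs to the description of the intervention.

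**Drop-off would show elsewhere.** Acceptance ratings are given at the end of each module and presented per module and arm, and missing values are counted, so falling numbers would be visible. This is a partial answer. The ratings come only from those who finish a module, and the counts form no criterion and have no CI.

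**Per-module tables belong in the SAP.** They may well be there. But the mismatch lies between an objective and a primary decision rule that this article itself fixes.

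**A stronger reading that the documents do not support.** A reader might infer that guidance turnaround makes non-completion likely for late enrolees, because feedback comes "within 1–2 working days after each module" and enrolment can be as late as 5 days before surgery. Nothing says that guidance must arrive before the next module can be opened. Patients work in their own time and modules take 20 minutes. Even if guidance did gate progress, module 3 would need only two earlier rounds, 2 × (1 to 2) = 2 to 4 working days, and the window runs up to 21 days. No distribution of enrolment times is given.

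**Conclusion.** The point holds. Criterion 2 measures uptake; objective 2 asks for more, and no other stated criterion or planned estimate supplies it. The worst case is a pass with 25.5% of module 1–3 completions delivered. That figure bounds what the rule permits and is not a forecast: it needs 49 patients to stop after one module. The graded figures rest on an assumed constant continuation rate that the article does not give. They show only that the chance of passing stays at 95.8% whatever the drop-off.

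The conclusion treats modules 1–3 as the best available reading of the intended minimum. It concerns intervention feasibility only; recruitment, retention and acceptance have their own criteria. The sample size arithmetic is sound. The article also does not support concluding that most patients will in fact miss modules 2 and 3.

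**What to change.** 1. Keep the at-least-one-module criterion and n = 64 per arm, and describe it as uptake, or starting the intervention.
2. Add a prespecified engagement estimate: per iEXPECT arm, the proportion of randomised patients who completed modules 1–3 by the day before surgery, with a two-sided 95% CI.
3. Draw the conclusion on engagement as intended from that estimate. If a threshold is wanted, the sponsor should set and justify it, bearing in mind that n = 64 may not support a lower limit of 75%.
4. Alternatively, reword objective 2 so that it asks only about uptake.
5. Report both rates by time from randomisation to surgery, in place of a sensitivity analysis that is only to be considered.

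The data should already be held: guidance is triggered by completion of each module, randomisation runs through REDCap, and surgery dates are recorded there. The cost is a few table rows and a protocol amendment in consultation with both ethics committees, with recruitment already started in November 2024. The feasibility statement may also turn out less favourable.
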